## Background e rationale

SARS-CoV-2 infection is characterized mainly by moderate/severe pneumonia associated with progressive endothelial damage and coagulopathy. Acute respiratory failure among COVID-19 occurs in 42% of patients with COVID-19 pneumonia, and 61–81% of patients requiring intensive care [1]. Among the suggested treatments for the management of ARDS patients, prone position (PP) can be used as an adjuvant therapy for improving ventilation in these patients, as recommended in the Surviving Sepsis Campaign COVID-19 guidelines [2-4]. The main rationale of PP is the recruitment of dorsal lung regions, increasing end-expiratory lung volume and chest wall elastane, decreasing alveolar shunt, and improving tidal ventilation [5]. In patients with severe ARDS, early application of prolonged PP sessions significantly decreased 28-day and 90-day mortality. The reduced mortality, however, is not only determined by an increase in arterial oxygen tension, but also by the beneficial effect of PP to reduce the damage associated with mechanical ventilation (VILI) [6-8].

PP can reduce mortality only if prescribed in case of severe impaired oxygenation, early, for prolonged periods, and associated to a protective ventilation strategy, as shown by the following meta-analyses. Munshi et al. [9] in a meta-analysis, evaluated the effect of prone positioning on 28-day mortality compared with conventional mechanical ventilation in supine position in adults with ARDS. The meta-analysis revealed no difference in mortality. However, subgroup analyses reported that PP can lead to a drop in the rate of mortality among patients with severe ARDS when applied to patients for least 12 hours a day. Mora-Arteaga et al. [10] In their meta-analysis, showed that PP can only reduce mortality in ARDS in the presence of: 1. low tidal volume ventilation; 2. PP onset within the first 48 hours; and 3. severe hypoxemia.

In a recent prospective cohort study performed in awake, non-intubated patients with COVID-19-related pneumonia and requiring oxygen supplementation [11], PP was feasible and effective in rapidly ameliorating blood oxygenation. The effect was maintained after resupination in half of the patients. Therefore, a careful patient selection, an adequate clinical protocol and pronation technique are essential to provide an effective treatment. Furthermore, prolonged pronation beyond the standard 16-18 hours has been proposed. Among those patients with longer prone ventilations (median time 36 hours), oxygenation seem to improve steadily [12]. The study was pivotal, carried on ten patients, and thus could only generate an

hypothesis, which is however clinically meaningful, identifying a novel approach that is starting to spread in critical care.

However, the adverse events of PP and the nursing workload should also be considered. Adverse effects associated with PP are several such as pressure ulcers (second-degree pressure sores or higher), bruising around the mouth due to presence of the tracheal tube, edema around the eyes and facial edema, endotracheal tube obstruction or accidental removal, limited access to the venous route, displacement of indwelling catheter and chest tube, gastroesophageal reflux, hyper-salivation, neuropathies, compression of nerves and retinal vessels [13].

## Objective

### *Primary Objective*

The primary objective of this study is to define potential clusters of critically ill patients – treated with PP – that are homogeneous in terms of both clinical and treatment characteristics.

### *Secondary Objectives*

Secondary objectives of this study are:

- 1) To assess the association between cluster membership and positive short-term outcome (i.e. an improvement in respiratory parameters)
- 2) To assess the association between cluster membership and positive long-term outcomes, defined here as 28days ventilator free days and patient survival at ICU discharge
- 3) To describe oxygenation, assessed by  $\text{PaO}_2/\text{FiO}_2$  ratio, before and after each PP manoeuvre
- 4) To describe the clinical circumstances under which clinicians opt for PP
- 5) To describe PP utilization rates in intensive care units in Italy
- 6) To describe PP in terms of treatment duration in intensive care units in Italy
- 7) To describe PP in terms of treatment timing in intensive care units in Italy
- 8) To investigate the impact of time of prone position ventilation on  $\text{PaO}_2/\text{FiO}_2$  ratios after each PP cycle and on days free from ventilation
- 9) To investigate the impact of PP on renal outcome

## Study design

This is an national, multicenter, non-profit, retrospective and prospective observational cohort study. The study is non interventional. Study duration is one year, starting presumably from 01/03/2021. Patients enrollment at each center will start at different times depending on the spread of the registry and local IRB approval. The first patient might be expected to be enrolled prospectively on 01/05/2021. Retrospectively patient might be enrolled since 01/12/2020. Final results of this study will be available in 01/05/2022.

### *Setting*

All patients undergoing PP at the participating centers will be retrospectively or prospectively enrolled. Patient enrollment will coincide with PP treatment start date (independently prescribed by the attending physician according to widely accepted guidelines and local clinical practice). Patients will be monitored and data recorded until hospital discharge. Post-discharge follow-up has not been envisaged.

This is an observational study: enrolled patients will not receive additional treatments other than those routinely administered in ICUs. Nonetheless, all parameters related to PP treatment will be recorded in the web-based registry and analyzed a posteriori to reveal potential correlations with patient outcomes.

### *Deviations from the study plan*

Any deviations from the present protocol will be reported to the local Institutional Review Board by the Principal Investigator through submission of an amendment request to be reviewed by IRB according to local/internal regulations.

### *Early termination and interruption of clinical evaluation*

Beside reporting the start and end dates of the study for monitoring purposes, the Principal Investigator will inform the IRB of the early termination of the study and inherent reasons.

## **Study population**

### *Inclusion criteria*

Adult patients (age >18 years) who meet all the following inclusion criteria may be included in this study:

1. Laboratory-confirmed COVID-19 infection
2. Prone positioning in patients admitted to ICU undergoing invasive Mechanical Ventilation

It should be underlined that the lack of consensus concerning the timing and duration of PP leads to variability in clinical practice and treatments are initiated in accordance with the judgement of the responsible physician. Under these circumstances, it is preferable to keep

inclusion criteria as wide as possible so as to obtain a real picture of the clinical practice worldwide.

#### *Exclusion criteria*

Besides contraindications to the Prone Positioning and patients in PP but undergoing Non-invasive ventilation should be excluded.

#### *Patient Withdrawal from Study*

Any patient may withdraw from this study at any time without prejudice to their care by directly informing the physician in charge of the registry. Patients do not have to disclose their reasons for withdrawal. Being an observational study, in case of patient withdrawal from study, his/her clinical pathway will remain unchanged.

### **Study outcomes**

#### *Primary Endpoint*

To identify profiles of patients in terms of outcomes according to specific patterns of PP and their intermediate surrogate endpoints.

#### *Secondary Endpoint*

Secondary endpoints of the study are:

1. Gas exchanges and respiratory mechanics before and after the first positioning manoeuvre, and during the early and late phase of the prone positioning. A positive response was defined a priori as an increase in  $Pao_2/Fio_2 \geq 20\%$
2.  $Pao_2/Fio_2$ , before and after each prone positioning manoeuvre. A positive response was defined a priori as an increase in  $Pao_2/Fio_2$  ratio  $\geq 20\%$ .
3. Duration of PP
4. ventilatory parameters (tidal volume, ventilatory frequency, PEEP, plateau pressure and static compliance of the respiratory system) after repeated prone positioning.
5. Mortality: ICU Mortality and Hospital mortality, 28-day free ventilator days
6. All Clinical variables at each PP cycle (as from the patient CRFs).
7. Clinical variables relevant to the application of PP treatment will be described, as well as timing of initiation of treatment. Specifically, absolute and relative frequencies of those clinical variables relevant to the application and timing of initiation of PP treatment will be described.

8. PP utilization rates (number of PP/ICU admissions) will be described in terms of yearly absolute frequencies and cumulative incidence among all the enrolled patients from all participating centers.

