#### *Data collection*

Data collection serves a scientific purpose. The data will be generated in the participating centers and recorded via a web application on the servers of the University of Padova using the study management software RedCap®.

Study data will be collected and managed using REDCap [15,16] electronic data capture tools, developed, tested, validated, and hosted at the Department of Cardiac-Thoracic-Vascular Sciences and Public Health, University of Padova, Italy. REDCap (Research Electronic Data Capture) is a secure, web-based software platform designed to support data capture for research studies, providing 1) an intuitive interface for validated data capture; 2) audit trails for tracking data manipulation and export procedures; 3) automated export procedures for seamless data downloads to common statistical packages; 4) procedures for data integration and interoperability with external sources.

Data will be recorded in the e-CRF only using coding procedures described in a separate document to comply with data protection applicable laws, including EU GDPR. A coding key reporting patient's name, surname, and date of birth will be filed only in local site files together with a subject screening and enrollment log.

In cases where a medical institution is interested in participation, an account in the RedCap platform is created. The data will be recorded using an encrypted data connection (HTTPS) in input masks via a web browser or mobile app. To ensure pseudonymized data analysis, each patient will be assigned a unique Subject ID (Patient Identification Number). RedCap is a secure web application for building and managing online databases. By using a hierarchical, role-based access concept, unauthorized access to the data will be impossible. Access to RedCap will be granted only to data collecting staff of participating centers, in accordance with the procedures outlined in the present protocol. These persons are bound to secrecy.

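### Endpoint 8 gives PP utilization two incompatible denominators: one yields 100% by construction, the other has no described data source

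*Protocol*

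**What the plan says.** Secondary objective 5 is "To describe PP utilization rates in intensive care units in Italy". The matching endpoint is item 8 under Secondary Endpoint in the protocol: "PP utilization rates (number of PP/ICU admissions) will be described in terms of yearly absolute frequencies and cumulative incidence among all the enrolled patients". Two populations appear in that one sentence. The bracket gives the ratio as "PP utilization rates (number of PP/ICU admissions", and the description that follows is "cumulative incidence among all the enrolled patients from all participating centers".

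Three sections fix who is enrolled:

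- **Setting:** "All patients undergoing PP at the participating centers will be retrospectively or prospectively enrolled", and "Patient enrollment will coincide with PP treatment start date".
- **Inclusion criterion 2:** "Prone positioning in patients admitted to ICU undergoing invasive Mechanical Ventilation".
- **Enrollment procedure:** it likewise makes invasive ventilation with prone position a condition of eligibility.

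The protocol describes data capture for enrolled patients only. The one possible trace of anyone else is a "subject screening and enrollment log", named under Data collection and filed locally at each site.

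**The concern.** A utilization rate needs a denominator that includes patients who could have been proned and were not. The registry's entry rule removes all of them. An analyst who follows the second half of endpoint 8 literally gets a number fixed by eligibility, with no information about practice. An analyst who follows the bracket needs admission counts that the protocol asks nobody to supply.

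The numerator is also unclear, because the number of PP could mean patients proned or PP sessions, and other secondary endpoints work per manoeuvre or per cycle.

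What is at stake is objective 5. The publication section foresees analyses every 6 months for abstracts or preliminary reports, so an uninformative rate could be reported early. An SAP could choose between the two denominators, but it could not create admission counts that were never requested.

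**Working it through.** The protocol states no utilization figure, so there is none to reproduce. The check compares the two ratios that endpoint 8 allows.

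**Inputs from the protocol**

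- Expected enrolment: 1000 patients in 100 centres (Sample size).
- Entry condition: invasively ventilated and proned (Inclusion criteria, Enrollment procedure).
- Entry date: start of PP (Setting).

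**Input not in the protocol**

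- The number of admissions in the denominator. I assume 1250, 2000 or 4000 per 1000 proned patients, for illustration only.

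**Step 1. Denominator = enrolled patients, numerator = patients**

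Cumulative incidence = (enrolled and proned) / enrolled = n/n = 1. For n = 1000 this is 1000/1000 = 100%, and it is the same for any n. There is also no time at risk before the event, because entry and event share a date.

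**Step 2. Denominator = enrolled patients, numerator = sessions**

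With k sessions per patient on average, the ratio is k × 1000 / 1000 = k. For k = 1, 2, 3 or 4 the result is 1, 2, 3 or 4. This is mean sessions per patient, never below 1, and it is not a utilization rate either.

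**Step 3. Denominator = admissions, numerator = patients**

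Rate p = 1000/N. Approximate 95% half-width = 1.96 × √(p(1 − p)/N), ignoring clustering by centre.

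| Assumed N | p = 1000/N | Half-width (points) | Value among enrolled |
|---|---|---|---|
| 1250 | 80% | 2.2 | 100% |
| 2000 | 50% | 2.2 | 100% |
| 4000 | 25% | 1.3 | 100% |

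The rate on admissions moves with practice. The value among enrolled patients does not.

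**Step 4. Is N available?**

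The sections on Setting, Follow-up procedure and Data collection describe records of enrolled patients. None asks for ICU admissions or for ventilated patients who were not proned. The screening log is not said to list non-proned patients. As proning is itself an eligibility condition, it may not list them.

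**Step 5. What survives**

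Yearly absolute counts of proned patients or sessions need no denominator and can be computed.

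**The case against.** The strongest reply is that the only ratio written out is the bracketed one, and its denominator is ICU admissions. On that reading, the mention of enrolled patients may only say whose PP events are pooled for the numerator, and the 100% does not arise. This stands in part. It would be wrong to say that the endpoint simply uses enrolled patients as its denominator, because the text names both. But a cumulative incidence among a group normally takes that group as its denominator, and the kinder reading still leaves the admissions denominator without a source.

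A second reply is that the case report forms are not shown and that admissions are an easily obtained centre-level figure. This also stands: the protocol describes no such collection, which does not prove that none takes place. A reader might infer that objective 5 can never be answered. The documents support only that it is not answerable as written.

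A reader might also infer that the yearly counts are distorted because the calendar years would contribute about 1, 12 and 2 months. That needs calendar-year bins, which endpoint 8 does not specify, and an end date of 01/03/2022. That date is inferred from a presumed start on 01/03/2021 plus one year, while the section on end of participation ties the study's end to the last patient's discharge. Staggered centre starts are disclosed under Study design. I do not rely on this argument.

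Finally, the endpoint is descriptive, one of eight secondary endpoints, and used neither in the primary clustering objective nor in the joint models. That is a fair reason to keep the severity down.

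**Conclusion.** The concern holds in this form: endpoint 8 names two incompatible denominators. The enrolled-patient one gives a per-patient cumulative incidence of exactly 100% by construction. The ICU-admission one has no described data source. Secondary objective 5 is therefore not answerable as written.

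The 100% follows from the entry rule and needs no numerical assumption. It applies to the per-patient cumulative incidence only, and the yearly absolute counts are unaffected.

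A reader might want to state the error in percentage points, for example by assuming that 30% to 80% of invasively ventilated COVID-19 admissions are proned, which would put it at 20 to 70 points. The documents do not support that figure. They give no true rate, and the protocol's bracket refers to ICU admissions, which is a broader group. The 25% to 80% in the working is likewise illustrative.

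Severity is moderate. One descriptive secondary objective is affected, and the primary objective is not.

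**What to change.** Amend endpoint 8 as follows:

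1. Delete the clause that places the cumulative incidence among enrolled patients.
2. Define the numerator as patients with at least one PP session.
3. State one denominator, counted per centre over that centre's enrolment period. It can be ICU admissions, as the bracket has it, or invasively ventilated COVID-19 ICU admissions, to match eligibility. The second changes the quantity now defined, so the sponsor should adopt it explicitly.
4. Have each centre report that denominator as an aggregate count from its admission register. The local screening log should not be assumed to serve, since it is not said to include non-proned patients.
5. Leave centres that cannot supply the count out of this endpoint only.

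If the counts cannot be obtained, drop objective 5 and keep the yearly counts as plain description.

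The cost is a wording amendment and one aggregate count per centre and period. No patient-level data on non-proned patients are needed.

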#### *Sample size*

Since this is an observational registry, no definite preliminary sample size calculation would be required. Considering the anticipated participation of 100 centers, an estimation of 1000 included patients seems reasonable.

#### *Enrollment procedure*

Adult patients of both sexes admitted to ICUs with COVID-19 admission diagnosis and who are in invasive mechanical ventilation with prone position will be considered eligible for enrollment.

#### *Follow-up procedure*

Clinical variables will be assessed and recorded during hospitalization only. Post-discharge follow-up has not been envisaged in this study.

#### *End of participation in the study*

At Hospital discharge, data collection and thus participation in the study will end for each respective patient. The scheduled end of the study is defined as the date on which the last enrolled patient is discharged, according to study duration.

### **Data management**

#### *Data property*

The individual data provided by a participating ICU are primarily the property of the ICU who generated the data. All investigators have the right to access their data at any time.

#### *Data collection*

Data collection serves a scientific purpose. The data will be generated in the participating centers and recorded via a web application on the servers of the University of Padova using the study management software RedCap®.

Study data will be collected and managed using REDCap [15,16] electronic data capture tools, developed, tested, validated, and hosted at the Department of Cardiac-Thoracic-Vascular Sciences and Public Health, University of Padova, Italy. REDCap (Research Electronic Data Capture) is a secure, web-based software platform designed to support data capture for research studies, providing 1) an intuitive interface for validated data capture; 2) audit trails for tracking data manipulation and export procedures; 3) automated export procedures for seamless data downloads to common statistical packages; 4) procedures for data integration and interoperability with external sources.

Data will be recorded in the e-CRF only using coding procedures described in a separate document to comply with data protection applicable laws, including EU GDPR. A coding key reporting patient's name, surname, and date of birth will be filed only in local site files together with a subject screening and enrollment log.

In cases where a medical institution is interested in participation, an account in the RedCap platform is created. The data will be recorded using an encrypted data connection (HTTPS) in input masks via a web browser or mobile app. To ensure pseudonymized data analysis, each patient will be assigned a unique Subject ID (Patient Identification Number). RedCap is a secure web application for building and managing online databases. By using a hierarchical, role-based access concept, unauthorized access to the data will be impossible. Access to RedCap will be granted only to data collecting staff of participating centers, in accordance with the procedures outlined in the present protocol. These persons are bound to secrecy.

#### *Data management and retention*

For data management, the study management software RedCap will be used. Name-related identification of individual patients by the documentation center (e.g., the University of Florence) is not required at any time during the study. During data collection and data processing, therefore, all necessary measures will be taken in order to establish de facto anonymization. The University of Padova will also be responsible for data storage. The data storage facilities are located in a locked, central room, accessible only to system administrators. Each participating center is granted access only to the patient data it has generated and recorded on the RedCap platform. Each participating center is expected to provide periodic ad hoc reports on the data it has collected.

### *Subsequent use of data*

SIAARTI and the steering committee, on behalf of the investigators, have the right to use all data that are pooled in the databank for scientific purposes. Investigators will be regularly informed about ongoing study activities. The steering committee and the SIAARTI Study Group have the right to access the data, pooled in the databank, for research purposes after the research project has been terminated, and with the approval of the SIAARTI Scientific Committee.

### *Archiving*

A copy of the electronic databank will be kept in Department of Cardiac-Thoracic-Vascular Sciences and Public Health, University of Padova, Italy and preserved for 5 years for subsequent use by SIAARTI and Steering Committee.

## **Statistical Analysis Plan**

All eligible patients enrolled in the registry will be included in the analyses. Continuous variables will be reported as median and Interquartile Range (IQR). Categorical variables will be reported as percentages. Statistical tests may be carried out for exploratory purposes, as appropriate.

Joint models will be used [14] to estimate the association of pronation with short- and long-term outcomes. Joint models consist of the simultaneous estimation of two statistical models that traditionally would have been estimated separately. The model will include the estimation of:

- 1) A longitudinal mixed-effects model that analyses changes in the respiratory parameters collected repeatedly during the ICU stay;
- 2) A survival or time-to-event model which analyses the time until the in-hospital death.

The joint estimation of these sub-models will be performed by assuming a mutual correlation between repeated observations through individual-level random-effects parameters.

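### The survival sub-model names in-hospital death as its only event although live discharge competes with it, and it does not analyse the long-term outcomes that the objectives define

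*Protocol*

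**What the plan says.** All references are to the Protocol.

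- **Statistical Analysis Plan.** Joint models are to be used "to estimate the association of pronation with short- and long-term outcomes". Their structure is given as "Joint models consist of the simultaneous estimation of two statistical models that traditionally would have been estimated separately": one longitudinal mixed-effects model for respiratory parameters, and "A survival or time-to-event model which analyses the time until the in-hospital death". No second event is named. The text mentions neither censoring nor competing events.
- **End of participation in the study.** "At Hospital discharge, data collection and thus participation in the study will end for each respective patient". Follow-up procedure confirms it: "Post-discharge follow-up has not been envisaged in this study". Setting says the same.
- **Secondary Objectives, item 2.** Long-term outcomes are defined as "28days ventilator free days and patient survival at ICU discharge". Item 8 uses days free from ventilation again.
- **Secondary Endpoint, item 5.** "Mortality: ICU Mortality and Hospital mortality, 28-day free ventilator days". There is no rule for counting ventilator-free days when a patient dies, goes home or is transferred before day 28.
- **Descriptive reporting** (Statistical Analysis Plan). "Categorical variables will be reported as percentages".

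**The concern.** Two things that the protocol fixes do not fit together.

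First, the event is death in hospital, and the observation window closes when the patient leaves hospital. Leaving alive is therefore not a loss of information about a death still to come; it makes the event impossible. A model with one event has to put discharged patients somewhere, and the usual place is censoring. The death hazard ratio that results compares the daily rate of death among those still in hospital. It says nothing about how long patients stay exposed to that rate. A cluster or pronation pattern that slows recovery keeps patients at risk for longer, so more of them die in hospital, and the death hazard ratio need not show it. That matters here because the secondary aim is to relate cluster membership to outcome.

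Second, the joint model is offered as the analysis of long-term outcomes, but its event is neither of the two outcomes that the objectives define under that name. Time to in-hospital death runs past ICU discharge, and ventilator-free days are not a time-to-death quantity.

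**Working it through.** The protocol gives no mortality rate, length of stay, hazard or event count, so there is no planned figure to reproduce. All hazards, mortality rates and lengths of stay below are assumptions for illustration, with constant daily hazards.

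**Formulas.** Let h_d be the daily hazard of in-hospital death and h_l that of live discharge.

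- Cumulative incidence of in-hospital death: CIF(t) = h_d/(h_d + h_l) × [1 − exp(−(h_d + h_l)t)]
- Risk read from a single-event model with discharge censored: 1 − KM(t) = 1 − exp(−h_d t)

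**Step 1: can the hazard ratio miss a difference in deaths?** Take h_d = 0.02 in both groups, so the death hazard ratio is 0.02/0.02 = 1.00.

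- h_l = 0.03: CIF(60) = 0.02/0.05 × [1 − exp(−3.0)] = 0.400 × 0.950 = 38.0%
- h_l = 0.015: CIF(60) = 0.02/0.035 × [1 − exp(−2.1)] = 0.571 × 0.878 = 50.1%

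The slower-discharge group has 12.1 points more in-hospital deaths with a hazard ratio of 1. Discharge hazards of 0.02 and 0.04 give the same pattern at day 90: CIF is 48.6% and 33.2%, while 1 − KM is 83.5% in both.

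**Step 2: how far off would an absolute risk be?** Let p be eventual hospital mortality and m the median stay. Then h_d + h_l = ln 2/m and h_d = p × ln 2/m. For p = 40% and m = 20 days, the total hazard is 0.0347 and h_d = 0.0139. At day 28, 1 − KM = 1 − exp(−0.388) = 32.2%, and CIF = 0.4 × [1 − exp(−0.970)] = 24.8%. The share discharged alive by day 28 is (1 − p) × [1 − exp(−28 ln 2/m)] = 37.3%.

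Selected combinations from p = 30, 40, 50, 60% and m = 15, 20, 30 days, including the extremes:

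| p | m (days) | Day 28: 1−KM / CIF | Excess (points) | Day 90: 1−KM / CIF | Excess (points) | Discharged alive by day 28 |
|---|---|---|---|---|---|---|
| 30% | 15 | 32.2 / 21.8 | 10.4 | 71.3 / 29.5 | 41.8 | 50.8% |
| 30% | 30 | 17.6 / 14.3 | 3.3 | 46.4 / 26.3 | 20.1 | 33.3% |
| 40% | 15 | 40.4 / 29.0 | 11.4 | 81.1 / 39.4 | 41.7 | 43.5% |
| 40% | 20 | 32.2 / 24.8 | 7.4 | 71.3 / 38.2 | 33.1 | 37.3% |
| 60% | 15 | 54.0 / 43.5 | 10.5 | 91.8 / 59.1 | 32.7 | 29.0% |
| 60% | 30 | 32.2 / 28.6 | 3.6 | 71.3 / 52.5 | 18.8 | 19.1% |

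The excess is about 3 to 11 points at day 28 and 19 to 42 at day 90.

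**Step 3: ventilator-free days for patients who leave before day 28.** Suppose patients discharged alive are counted as off the ventilator to day 28. Assume that 15-45% of all patients leave early, that 1-5% of these die or are ventilated again by day 28, and that each such patient is credited with 14 days too many. The mean is then too high by 0.15 × 0.01 × 14 = 0.02 days up to 0.45 × 0.05 × 14 = 0.3 days.

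**Step 4: does the model match the objective?** Secondary Objectives item 2 asks for ventilator-free days and survival at ICU discharge. The only event analysed is in-hospital death. Neither outcome has an association analysis named for it.

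**The case against.** The strongest reply is that the protocol never says discharge will be censored. It names the event and stops, and the handling of competing events and the derivation of endpoints are commonly left to a separate statistical analysis plan, which was not available for this review. Moreover, a cause-specific death hazard ratio is a legitimate quantity, and a value of 1.00 in Step 1 is correct for what it measures. Much of this stands. Censoring is an inference from a single-event model, and the defect is an incomplete analysis, not an invalid one. What remains is that the protocol's own analysis section commits to two sub-models and one event.

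A reader might go further and infer that the study will overstate mortality. The document does not support that. No Kaplan-Meier curve or model-based absolute risk is planned. ICU and hospital mortality are categorical and would be reported as percentages, and status at discharge is observed for every patient followed to discharge, so these figures carry no such bias. The excesses in Step 2 apply only if someone reads a risk off the model.

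A reader might also infer that the 28-day endpoint cannot be measured without further follow-up. For patients who go home alive, a counting rule is enough, and Step 3 suggests the remaining error is small. Patients transferred while still ventilated are the exposed group, but the protocol does not say how many there are or how they are coded, and the case report form is not shown.

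**Conclusion.** The point holds in a limited form. The protocol fixes a single-event model for in-hospital death while observation ends at discharge, and it does not recognise live discharge as a competing event. If discharge is censored, the model can show no difference in death hazard between groups whose in-hospital mortality differs materially (38.0% against 50.1% at day 60 in the assumed example), and absolute risks taken from it would be too high by the ranges above. These sizes rest on assumed constant hazards and assumed mortality and length of stay. The direction does not depend on the particular values.

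Independently of any assumption about censoring, the sub-model does not analyse the two long-term outcomes in Secondary Objectives item 2, and the protocol gives no counting rule for ventilator-free days.

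This concerns secondary, associational aims in a registry whose primary objective is to define clusters. It is worth correcting before analysis. It does not undermine the crude mortality figures or the study as a whole.

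**What to change.** In the Statistical Analysis Plan section of the protocol:

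1. Specify the joint model with two competing events, in-hospital death and live discharge. Report the effect on each cause-specific hazard, with the cumulative incidence of both events.
2. Add analyses of survival at ICU discharge and of 28-day ventilator-free days, so that Secondary Objectives item 2 is answered by a named analysis.
3. State the ventilator-free-day rule: death by day 28 counts as zero days; a patient discharged home alive counts as ventilator-free from discharge to day 28; a patient transferred while ventilated is identified from the status recorded at transfer and is not counted as ventilator-free.

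If a separate statistical analysis plan already contains these, aligning the protocol text is enough.

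The cost is modest extra modelling and one event code. Ventilation status at transfer falls within the present observation window, so at most it needs a field on the case report form. No new follow-up after discharge is needed. Obtaining day-28 status from receiving hospitals would reverse the sections on follow-up and end of participation and require ethics amendments across an anticipated 100 centres. That is not cheap, and this fix does not depend on it.
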